### Experimental chronology

According to the type of CLP and the healthcare facility involved, the time lapse between diagnosis and the first surgery varies from birth to six months. Two evaluation times are planned:

· T0, when the infant is 4 months

· T1, when the child is 12 months, i.e. 6 months or more after the first surgical intervention

The choice of positioning T0 at 4 months is based on the following arguments:

· Because of the variability of the protocols used by the surgical teams in each of the centres, it is not possible to define T0 and T1 that correspond to a specific examination for all the centres;

· At this age, the children for whom the surgery occurs early have already had their operation. They can therefore be compared to children whose operation is to occur subsequently (up to 6 months), the two groups comprising roughly equivalent numbers. In a more detailed analysis, it will be possible to compare the children receiving surgery at birth with those receiving surgery at three months or more.

The choice of positioning T1 at 12 months is justified by the following argument:

· When the child is one year old, this is sufficiently distant from both birth and the first surgical intervention (by at least six months) to enable a repeat of examinations and questionnaires used in the first stage of the study. This will enable comparison of psychological perceptions of the parents and the relational development of the child between T0 and T1, as well as exploration of the question of the timing of surgery.

### Inclusion criteria

Only children with CLP are included, either isolated or familial, syndromic or nonsyndromic. Parents are included following informed consent for themselves and their child.

Two subgroups of children are also formed with respect to the time of diagnosis: 

Sub-group 1: parents having received an antenatal diagnosis

Sub-group 2: parents having discovered the diagnosis at childbirth.

For both subgroups it is in the course of the post-natal consultation that the surgical team approaches parents to enter the study, after providing all required information, and without interfering in any way with the treatment protocol.

### Non-inclusion criteria

Non-inclusion criteria are:

children with CP alone

children born before 36 weeks amenorrhoea

children whose birth weight was under 2.5 kg

children placed in foster homes

parents under legal guardianship

parents insufficiently conversant with French and/or illiterate

### Criteria for removal from the study

refusal to participate by one of the child's parents in the course of the study follow- up

the occurrence of a complication in the course of treatment and/or a serious illness requiring major specific treatment

an unexpected complication in connection with the surgical intervention

serious illness or death of one of the parents

the parents moving house outside the regions involved in the research

### Data collection

The documents collected directly in the observation file for each child concern the following:

· Tests and examinations performed at T0 and T1

· Brief analysis of the individual situation of the persons present performed by the psychologist present at times T0 and T1

· Information sheet drawn up by the surgeon giving the precise type of CLP, the time when diagnosis occurred, family history, the pregnancy, care provision to the child, and also the surgeon's impression of the relationship established with the parents

· Any undesirable event

## Statistics

### Description of the statistical methods to be used

The ADBB score measured at 12 months is used as the main criterion to compare children receiving early intervention with those receiveing a later intervention. Likewise, for the parents, the PSI scores are compared between the early and later intervention groups.

A descriptive analysis of the variables will be performed. The mean, median, standard deviation and range will be provided for continuous variables, as well as proportions for categorical variables, along with 95% confidence intervals.

Scores for infant withdrawal and parental stress (ADBB and PSI in particular) will be analysed in relation to the time-lapse (two groups) before surgery (Wilcoxon-Mann- Whitney non-parametric test).

The correlations between ADBB scores and the different measures among parents (in particular PSI scores) will be studied using the Spearman correlation coefficient.

A multivariate analysis (multiple regression after transformation, where needed, of the dependent variable) will be performed to take into account the variables affecting the scores.

For all the analyses, an adjustment will be performed to take into account the type of cleft (labial cleft alone, or labial cleft with cleft palate) and whether it is unilateral or bilateral.

The analyses will be performed with SAS statistical software, release 9.2., SAS Institute Inc., Cary, NC, USA).

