## Methods/Design

### Main hypothesis

The main hypothesis of this research is that the longer the time lapse before the first surgical intervention, the more likely are parental perceptions and feelings to upset the parent–child relationship and affect the harmonious development of the child.

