### Level of statistical significance

The significance level is set at 5% for all analyses. Differences corresponding to a p- value under 5% will be considered statistically significant. All tests will be two-sided.

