### Number of subjects to include and justification

The number of subjects to include is estimated on the basis of a main comparison of two groups, an early intervention group and a later intervention group. For the ADBB score, the validation studies showed a standard deviation of 3.78.

Considering that a difference of 2 units in this score is clinically significant, in a two-sided test, with a type 1 error of 5%, the number of subjects required to show a difference of this magnitude with a power of 90% is 75 in each group, 150 in all. For the PSI (Parenting Stress Index), the reference studies estimated a standard deviation of 41.9 with a mean of 229. With 150 subjects, in a two-sided test, it will be possible to evidence a difference between the two groups of 10% (half a standard deviation) with a power of 90%.

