## Discussion

### Main objectives

The aims of this research are:

1) to evaluate any affective withdrawal of infants with CLP in relation to the mental state of the parents and the waiting time before the first surgical repair intervention

2) to improve knowledge concerning the psychological effects on parents of the malformation itself, of the type of therapeutic provision in terms of time lapse between diagnosis and first surgery, of relationships with the members of the healthcare team, and of the family and social environment. In an ethical perspective, data on the time-lapse to instatement of treatment in the different protocols and the effects in each case are recorded and analysed and will serve to improve the quality of information provided during the waiting period, and the quality of the support given to the parents and the child by the healthcare team prior to the first surgical intervention. This will enable new protocols to be developed so as to minimise the psychological impact on parents as far as possible, and improve treatment of these children in the long term.

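### The ADBB–parent Spearman correlations are adjusted for cleft features but not for surgery timing, which can raise their false-positive rate for a within-group link from 5% to about 11–13%

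*Protocol article*

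**What the plan says.** All references are to the Protocol article. Under Main objectives, the first aim is "to evaluate any affective withdrawal of infants with CLP in relation to the mental state of the parents and the waiting time" until first repair. The Main hypothesis includes a parent-to-child step: the longer the wait, "the more likely are parental perceptions and feelings to upset the parent–child relationship and affect the harmonious development of the child".

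Under Description of the statistical methods to be used, four statements bear on this point:

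- The infant and parent scores "will be analysed in relation to the time-lapse (two groups) before surgery", so both main criteria are compared between the same two timing groups.
- On the parent–child link: "The correlations between ADBB scores and the different measures among parents (in particular PSI scores) will be studied using the Spearman correlation coefficient". Stratification by timing group is not mentioned here.
- A regression model is also planned: "A multivariate analysis (multiple regression after transformation, where needed, of the dependent variable) will be performed to take into account the variables affecting the scores". No covariates are listed.
- The blanket rule reads: "For all the analyses, an adjustment will be performed to take into account the type of cleft", and laterality is added to it. Neither timing group nor centre is named.

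Under Level of statistical significance: "The significance level is set at 5% for all analyses". The correlations are therefore open to testing at that level.

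The sample-size section takes an ADBB SD of 3.78 and continues: "Considering that a difference of 2 units in this score is clinically significant". It also gives a 10% (half-SD) PSI difference as detectable with the same 150 subjects.

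**The concern.** Under the study's hypothesis, surgery timing acts on both the infant's score and the parents' scores. Two variables that each differ between the same two groups will correlate when the groups are analysed together, even if they are unrelated inside each group. The adjustment set named for all analyses does not remove this, because it omits timing.

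The correlation is the natural evidence for the parent-to-child step. A significant coefficient could be read as showing that stressed parents have more withdrawn infants, when all it reflects is that waiting moved the two scores separately. The larger the true timing effect on both criteria, the stronger this artefact becomes.

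**Working it through.** **Inputs from the sample-size section.** ADBB difference 2, SD 3.78; PSI mean 229, SD 41.9, difference 10% or half an SD; 75 per group; 5% two-sided; power 90%.

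**The plan's own figure.** n per group = 2 × (1.960 + 1.282)² × 3.78² / 2² = 75.1. Rounded up this is 76, and 75 per group gives power 0.900, so the stated 75 is reproduced. For PSI, 10% of 229 is 22.9, or 22.9/41.9 = 0.547 SD (power 0.917). Exactly half an SD is 20.95 (power 0.865). Both PSI values are carried below. The document gives no figure for the correlation analysis.

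**Scenario (an assumption, not a figure from the document).** No ADBB–PSI correlation within either timing group, normal scores with equal variances, one parent score per child, no dropout.

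**Induced correlation.** With equal groups and standardised shifts d1 and d2,

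r = (d1 × d2 / 4) / √[(1 + d1²/4)(1 + d2²/4)].

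- d1 = 2/3.78 = 0.529, d2 = 0.547: r = 0.0723 / √(1.0700 × 1.0747) = 0.067.
- d1 = 0.529, d2 = 0.500: r = 0.0661 / √(1.0700 × 1.0625) = 0.062.

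**Against the critical value.** At n = 150, two-sided significance needs |r| of about tanh(1.96/√147) = 0.160. The induced value is well below that but moves the test statistic off zero. By Fisher's z, the shift is atanh(0.067) × √147 ≈ 0.82 standard errors, giving a rejection rate of 13.0%. For r = 0.062 it is 11.7%.

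**Simulation, 40,000 trials per scenario, no within-group link.** The partial version centres the ranks within timing group before correlating.

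| Shifts (ADBB, PSI, in SD) | Unadjusted Spearman rejects | Partial on timing rejects |
|---|---|---|
| 0, 0 | 5.0% | 5.0% |
| 0.529, 0.547 (design) | 12.9% | 5.1% |
| 0.529, 0.500 (design) | 11.3% | 5.1% |
| 0.265, 0.250 (about half) | 5.4% | 4.9% |
| 0.529, 0 (ADBB only) | 5.1% | 5.1% |
| 0.794, 0.820 (1.5 times) | 40% | 5.2% |

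At the first design setting, a 100:50 split gives 11.0%, and rounding ADBB with a floor at zero gives 12.5%. The 1.5-times row lies beyond any effect stated in the plan and only shows the direction of travel.

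The simulation applies no cleft adjustment. That adjustment would remove the timing shift only so far as cleft type and timing group are associated.

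**Does adjusting for timing hide a real link?** Timing is treated here as upstream of both scores, so conditioning on it leaves any parent-to-child path in place. A separate simulation of 4,000 trials, with ranks centred within centre and a true within-group correlation of 0.25, gave power of 83%.

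**The case against.** The strongest case on the other side has five parts.

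- **The article does not say the coefficient is pooled.** It condenses a fuller protocol, and presentation by group may be settled elsewhere. It is true that pooling is inferred. But the article does say what all analyses are adjusted for, and timing is not in that list. A single coefficient adjusted for cleft features is the natural reading.
- **The regression is meant to take account of variables affecting the scores.** On this point's own premise, timing is such a variable. This stands in part: a timing-adjusted link may well be produced. A reader might infer that none will be, and the document does not support that. Equally, it does not name timing as a covariate, and the regression does not alter the Spearman coefficient or its p-value.
- **The shifts are design targets, not forecasts.** This stands. The second secondary hypothesis expects the later group's negative feelings to come closer to the early group's, and the child's distress to fall, over time. If so, the artefact would be smaller at 12 months. The correlation sentence names no visit.
- **A marginal association is a legitimate description.** This also stands, provided it is labelled as such. It cannot by itself separate a parent-to-child link from two separate effects of waiting.
- **The main criteria are the group comparisons, and nothing makes the correlation decisive.** That is fair, and it limits the consequence. The correlation still addresses the first main objective and falls under the 5% level.

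A reader might also infer that the test will come out significant without any within-group link. It would not, as a rule: at the design shifts about 87 to 89% of such trials would not reject, and about 1,700 to 2,000 families would be needed for the shifts alone to give 80% rejection.

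**Conclusion.** The point holds in a limited form. As written, the ADBB–parent correlations are not adjusted for the exposure under study. If timing moves both scores by the differences the study is sized to detect, and there is no link within timing groups, the false-positive rate for such a link is about 11 to 13% instead of 5%, with an expected coefficient of 0.06 to 0.07. That is roughly 2.3 to 2.6 times the nominal level.

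The result depends on both scores shifting in the same direction by about those amounts. It largely disappears at half of them, or if only one score moves. The documents support neither a claim that a significant correlation would necessarily be an artefact nor a claim that the plan has no means of adjusting for timing. The change is worth making because the analysis serves a main objective and the remedy needs no new data.

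**What to change.** Under Description of the statistical methods to be used, state that the correlations between ADBB and the parent measures are adjusted for surgery-timing group as well as cleft type and laterality, using a partial or stratified Spearman coefficient. Show the coefficient within each timing group beside it.

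Centre can replace timing group, since it carries timing. According to Recruiting centres, the sites also differ in whether a psychologist is permanently available, which could affect both scores. If the unadjusted coefficient is kept, label it descriptive and do not use it alone as evidence of a parent–child link.

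The cost is one sentence of wording and a PARTIAL statement in the SAS correlation procedure. It uses 1 degree of freedom for two timing groups, or 3 for four centres, out of 150 families. The reported coefficient may be slightly smaller.

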### Level of statistical significance

The significance level is set at 5% for all analyses. Differences corresponding to a p- value under 5% will be considered statistically significant. All tests will be two-sided.

### Dealing with missing data

Particular care will be taken to ensure that the questionnaires are satisfactorily completed, in particular where a score is to be calculated. In case of missing values, the already validated rules for replacement of missing data determined for each scale or questionnaire will be used. If necessary, for the variables considered important for the detailed analyses, multiple imputation procedures will be used.

### Number of subjects to include and justification

The number of subjects to include is estimated on the basis of a main comparison of two groups, an early intervention group and a later intervention group. For the ADBB score, the validation studies showed a standard deviation of 3.78.

Considering that a difference of 2 units in this score is clinically significant, in a two-sided test, with a type 1 error of 5%, the number of subjects required to show a difference of this magnitude with a power of 90% is 75 in each group, 150 in all. For the PSI (Parenting Stress Index), the reference studies estimated a standard deviation of 41.9 with a mean of 229. With 150 subjects, in a two-sided test, it will be possible to evidence a difference between the two groups of 10% (half a standard deviation) with a power of 90%.

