### Current state of the study

The study started in March 2010 and should be completed in the course of the second semester 2012. More than one hundred families of the 150 required have been included, among whom 18 have already been assessed at T0 and T1. The preliminary results cannot for the moment be reliably interpreted. However, concerning inclusions, it can be noted that certain parents refused to participate in this study. These refusals are mainly attributable to firstly the distance between home and the healthcare centre or the evaluation premises, and secondly to the repeated visits required for the care of the child, and also certainly to the reluctance of parents to confide their feelings and difficulties since the discovery of the malformation. As the study cannot intrude on the private lives of these families, it is impossible to press for agreement, especially in cases where the refusal is from one parent only. As for the evaluations, as mentioned earlier, in the literature the parent–child relationship is always studied by interviewing the parents. The choice and the relevance of the questionnaires used can be questioned. Indeed, self-administered measures are subject to caution, as parental responses can lack objectivity. The contribution of the ADBB scale for children in this age group in this instance enables the study of the parent- child relationship in a symmetrical manner, and also more objectively. The behaviour of an infant and any signs of withdrawal are unlikely to be dissimulated, which may not be the case with the parents.

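### The 150 families to be included are the number that must be evaluable at 12 months for about 90% power; nothing is added for the removals the protocol lists

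*Protocol article*

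**What the plan says.** The protocol article, under Number of subjects to include and justification, sizes the study on the comparison of an early and a later intervention group. It takes the variability from earlier work ("For the ADBB score, the validation studies showed a standard deviation of 3.78") and sets the target difference ("Considering that a difference of 2 units in this score is clinically significant"). From these it concludes that the number of subjects required "with a power of 90% is 75 in each group, 150 in all".

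The test settings are in Level of statistical significance: "The significance level is set at 5% for all analyses" and "All tests will be two-sided". Under Description of the statistical methods to be used, the main criterion is the ADBB score at 12 months, and the two groups are compared with a Wilcoxon-Mann-Whitney test.

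Two further sections bear on what the 150 counts:

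- Criteria for removal from the study lists five grounds. The first is "refusal to participate by one of the child's parents in the course of the study" follow-up. The others are a treatment complication or serious illness, an unexpected surgical complication, serious illness or death of a parent, and moving out of the regions involved.
- Current state of the study reports that "More than one hundred families of the 150 required have been included". So 150 is a count of families entering the study.

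**The concern.** Power depends on the number of children whose 12-month score enters the comparison. The protocol attaches its 90% to the number of families included. The two numbers agree only if every included family is assessed at 12 months, yet the protocol sets out five ways in which a family can leave before then.

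The stated power is what a reader would use to weigh a non-significant result. If the type II error for a difference that the protocol calls clinically significant is above the implied 10%, a null finding on the timing of surgery would be given more weight than it deserves.

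**Working it through.** **Inputs from the protocol.** Difference 2 ADBB units; SD 3.78; two-sided 5%; power 90%; equal groups. Equal sizes are implied by 75 in each group, and Experimental chronology expects "the two groups comprising roughly equivalent numbers".

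**Input not in the protocol.** The proportion of included families not assessed at 12 months. I use 0, 5, 10 and 20% as assumptions, spread equally over the groups.

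**Step 1: reproduce the stated figure.** Normal formula for two means:

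n per group = 2 × (z₀.₉₇₅ + z₀.₉₀)² × (SD / difference)² = 2 × (1.960 + 1.282)² × (3.78 / 2)² = 2 × 10.507 × 3.572 = 75.07

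The protocol's 75 is this value to the nearest whole number; rounding up would give 76. The figure is reproduced, and it contains no addition for losses.

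**Step 2: power at the stated size.** With 75 per group the noncentrality is 2 / (3.78 × √(2/75)) = 3.240 on 148 degrees of freedom. The normal formula gives 90.0% and the noncentral t gives 89.6%.

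**Step 3: power after losses.** With loss d, the evaluable number per group is m = 75 × (1 − d), the noncentrality is 2 / (3.78 × √(2/m)), and the degrees of freedom are 2m − 2.

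| Assumed loss | Evaluable per group | Noncentrality | Power, t-test |
|---|---|---|---|
| 0% | 75 | 3.240 | 89.6% |
| 5% | 71.25 | 3.158 | 88.0% |
| 10% | 67.5 | 3.074 | 86.2% |
| 20% | 60 | 2.898 | 82.0% |

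At 20% loss the type II error is 18.0%, against the 10% implied.

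**Step 4: does the planned test change the picture?** For normal scores the Wilcoxon test has relative efficiency 3/π = 0.955. Putting 0.955 × m in place of m gives 88.2% with no loss, 86.5% at 5%, 84.6% at 10% and 80.2% at 20%, which is 1 to 2 points below the t-test. A simulation of 10,000 runs with normal scores gave 88.7% at 75 per group and 80.3% at 60. With right-skewed scores of SD about 3.78 and a 2-unit mean difference (assumed shapes), simulated Wilcoxon power was about 97% at 75 per group and about 93% at 60. The direction of the Wilcoxon effect therefore depends on a distribution that the protocol does not give.

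**The case against.** The calculation itself is right: 75.07 against 75 stated. The article condenses a fuller protocol, which might provide for replacing removed families. No loss rate is documented, and some of the removal grounds may be rare. At 5% loss the shortfall is about 2 points, and even at 20% power stays above 80%. If ADBB scores are skewed, the planned test could keep 90% power despite such losses.

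Most of this stands, and it limits the point. It does not remove it. An allowance for losses cannot be hidden inside an inclusion number that equals the evaluable number. Replacement of removed families would take inclusions above the 150 that the article gives as required.

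A reader might be tempted by stronger readings that the document does not support:

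- **The Wilcoxon test makes 75 per group too few.** Under normality it costs 1 to 2 points, which is not a defect by itself, and with skewed scores it may gain power.
- **The burdens described in Current state of the study show dropout.** Distance, repeated visits and reluctance to confide are given there as reasons for refusing to enter. Families who refuse are never among the 150, and no follow-up loss is reported.
- **A badly unequal split, such as 50/100, erodes power further.** The protocol expects roughly equal groups, and nothing in it points to such a split.

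**Conclusion.** The point holds as a mislabelled number with a modest effect on the stated power. The 150 is the evaluable number from a two-means calculation, used as the enrolment target, with nothing added for the removals that the protocol itself provides for. On the inputs used for sizing, power for a 2-unit ADBB difference is 89.6% if every family is assessed at 12 months, and about 82–88% if 5–20% are not.

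This rests on normal-theory inputs, equal groups, and loss rates that are assumed. It does not show that the sample size arithmetic is wrong, that the study is seriously underpowered, or that the planned test would fall below 90% whatever the shape of the scores.

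**What to change.** In Number of subjects to include and justification, describe 75 per group as the number evaluable at T1. Then restate the power, for example: 150 families will be included; if 5–20% are not assessed at 12 months, power to detect a 2-unit ADBB difference is about 82–88% under the normal-theory inputs used for sizing. If the sponsor has its own expected loss rate, that rate and its power should replace the range.

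The cost is a sentence or two and a slightly less favourable stated power. It needs no added enrolment and no change to the analysis.

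### The PSI power sentence treats a 10% difference as half a standard deviation; its 90% power holds for the former (0.55 SD), but half an SD has only about 84–86%

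*Protocol article*

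**What the plan says.** All the figures are in the protocol article, under Statistics.

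- **Number of subjects to include and justification** derives the sample size from the infant withdrawal score (ADBB): "For the ADBB score, the validation studies showed a standard deviation of 3.78". A 2-unit difference is the target ("Considering that a difference of 2 units in this score is clinically significant"), and the number required for 90% power "is 75 in each group, 150 in all".
- The same section then checks that this number also serves the PSI. It gives the inputs ("the reference studies estimated a standard deviation of 41.9 with a mean of 229") and says what can be detected: "With 150 subjects, in a two-sided test", "a difference between the two groups of 10% (half a standard deviation) with a power of 90" per cent.
- **Level of statistical significance**: "The significance level is set at 5% for all analyses", with all tests two-sided.
- **Description of the statistical methods to be used**: the ADBB and PSI scores "will be analysed in relation to the time-lapse (two groups) before surgery", by the Wilcoxon-Mann-Whitney test.

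**The concern.** The bracket makes 10% and half an SD the same quantity. That would be true only if the SD were 20% of the mean. On the stated figures it is 41.9 / 229 = 18.3%, so the two differ, and one power cannot be exact for both.

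The PSI is one of the two main criteria, and this sentence is the article's only support for the sample being adequate for it. Half an SD is also the figure that a reader is likely to carry forward when interpreting a non-significant result. If the 90% belongs to the larger difference only, the chance of missing a half-SD difference is 14–16%, not 10%.

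**Working it through.** **Inputs.** From the sample-size section: PSI mean 229, SD 41.9, 75 per group; ADBB SD 3.78, difference 2. From the significance section: two-sided 5%. From the methods section: Wilcoxon-Mann-Whitney test on two groups. No allowance for loss is used.

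**1. The ADBB sample size.** n per group = 2 (z₀.₉₇₅ + z₀.₉₀)² SD² / difference² = 2 × (1.960 + 1.282)² × 3.78² / 2² = 75.07. This agrees with the stated 75 (76 if rounded up), so the basis of the 150 reproduces.

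**2. The two PSI differences.**
- 10% of the mean: 0.10 × 229 = 22.9 points; 22.9 / 41.9 = 0.547 SD.
- Half an SD: 0.5 × 41.9 = 20.95 points; 20.95 / 229 = 9.15% of the mean.
- Gap: 22.9 − 20.95 = 1.95 points.

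**3. Power at 75 per group.** Normal approximation: power = Φ(d √(n/2) − 1.960), where d is the difference in SD units and √(75/2) = 6.124.
- d = 0.547: 0.5465 × 6.124 = 3.347; Φ(1.387) = 91.7%.
- d = 0.5: 0.5 × 6.124 = 3.062; Φ(1.102) = 86.5%.

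The t-test figures use the noncentral t distribution with 148 degrees of freedom. The Wilcoxon figures use the same calculation with n multiplied by the test's efficiency under normality, 3/π = 0.955, which gives an effective 71.6 per group.

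| Difference | SD units | Normal approximation | t test | Wilcoxon |
|---|---|---|---|---|
| 22.9 points (10%) | 0.547 | 91.7% | 91.4% | 90.1% |
| 20.95 points (half an SD) | 0.500 | 86.5% | 86.0% | 84.4% |

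The stated 90% reproduces for the 10% difference, almost exactly with the planned test. It does not reproduce for half an SD by any of the three methods.

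**4. What 75 per group detects with 90% power.** By t test, 22.3 points (0.533 SD, 9.7% of the mean). By Wilcoxon, 22.85 points (0.545 SD, 9.98% of the mean), which is in effect the article's own 10%.

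**5. Could another convention rescue the half-SD reading?** A one-sided test would give half an SD about 92% power, but the article specifies two-sided tests. Unequal groups lower both powers: a 60/90 split gives 90.6% for the 10% difference and 85.1% for half an SD (normal approximation).

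**The case against.** The strongest defence is that the detectable difference is stated as 10% and the bracket only paraphrases it. On that reading the sentence is right, and for the test actually planned it is right almost to the decimal (90.1%). Calling 0.55 SD half a standard deviation is loose rounding, 1.95 points on a scale with an SD of 41.9. The article names no clinically important PSI difference of half an SD; it uses that language only for the 2-unit ADBB difference. Most of this stands, and it is why the point is minor. It does not clear the bracket: the mean and SD stand in the sentence before, the two readings fall on opposite sides of 90%, and the half-SD reading misses by 4 to 6 percentage points.

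Three stronger readings are tempting, and the document does not support them.

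- A reader might infer that the 90% is wrong on either reading. It is not: the 10% difference has 91.4% power by t test and 90.1% by Wilcoxon, and either supports a stated 90%.
- A reader might infer that 150 is too few. Half an SD would need 85 per group for 90% power (normal approximation), but the 150 was set by the ADBB calculation, which reproduces. The PSI sentence is a check on a number already fixed.
- A reader might want to lower the PSI power further for loss to follow-up. The article gives no loss rate to use, and that question is separate from the inconsistency here.

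**Conclusion.** The concern holds in a limited form, and its severity is minor. The sentence gives one power to two different effect sizes. The 10% difference (22.9 points, about 0.55 SD) has about 90% power, as stated. A half-SD difference (20.95 points, 9.1% of the mean) has about 86% power by t test and 84% by the planned Wilcoxon test, so the type 2 error for it is 14–16%. The sample size, tests and endpoints are unaffected.

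The figures assume that the 10% is taken of the stated mean of 229 (the article does not name the base, but no other is offered), 75 analysed per group, a common SD of 41.9, a two-sided 5% test and, for the Wilcoxon figures, roughly normal scores.

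**What to change.** Correct the bracket and leave the rest of the sentence as it is. Keep 10% and 90%, replace the half-standard-deviation wording with *22.9 points, about 0.55 SD*, and add one clause: *a difference of half a standard deviation (20.95 points) has about 84–86% power (Wilcoxon and t test respectively)*.

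The alternative of restating the 90%-power difference as 22.3 points (0.53 SD) is not advised. That is a t-test value and slightly optimistic for the planned Wilcoxon test, for which the existing 10% is already correct.

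The cost is one edited sentence and a slightly less favourable standardised effect size. The number of families does not change.
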